#### 6.1.3 *Other study parameters*

Anthropometric measurements including height and weight will be measured. Height and weight measurements will be used to determine individual BMI scores.

## 6.2 Study Procedures

### *Information Session and Screening:*

After expressing interest in taking part in the study, all potential participants will be invited to an initial information session. During this information session, subjects who fulfil the general requirements of the study will be asked to undergo a standard SBP and DBP measurement. Subjects with a blood pressure lower than 125 mmHg at the information session will be excluded from the study.

All potential participants who meet the blood pressure criteria at the information session will be given a short medical history and lifestyle questionnaire as well as informed consent form which they will be allowed to fill in at home and will be invited back for a screening session at the university. Prior to the screening session, participants will be asked to collect 24-hour urine samples. This will be done to determine the level of protein and albumin in the urine. Bottles for urine collection will be provided to all participants.

During the screening itself, height, weight and blood pressure will be measured and blood samples will be taken during the screening session. **If a blood pressure score above 160mmHg is measured during the screening session then subjects will be advised to contact their General Practitioner and will not be eligible for participation.** Blood samples taken during the screening session will be used to analyse biochemical parameters of general health including kidney and liver function – as stated in the inclusion criteria. Finally, subjects will be tested for feasibility of ultrasound image acquisition on the brachial artery.

### *Run-in:*

Based on the medical history and lifestyle questionnaire as well as the screening measurements, 40 eligible participants will be selected and enrolled onto the study. Prior to the initiation of the first intervention arm, each subject will complete a one-week run-in period. During this run-in period, participants will be asked to restrict their consumption of flavonoid-rich foods (see Appendix I). This dietary advice will be maintained throughout the study period.

### **Part 1**(Supplement Study):

During the 24-hour period preceding the first measurement day, participants will be asked to collect 24-hour urine samples and 24-hour ambulatory blood pressure will be measured. Instructions and bottles for urine collection as well as blood pressure monitors will be provided. Participants will return the blood pressure monitors when they visit the university for the measurement day.

Baseline measurements of all parameters will be taken on the morning of the first study day, following an overnight fast ( $T_0$ ).

Upon completion of the first study day, participants will be asked to consume two supplements per day for the following 4 weeks before returning for follow-up assessments ( $T_1$ ). Follow-up assessments will be carried out at the same time of day as the baseline measurements, following an overnight fast and will include the same measurements as the baseline measurements. This means that weight, FMD, PWA, PWV, blood pressure and microcirculation vasomotion will be measured and blood samples will be taken for all participants. After follow-up measurements have been taken, subjects will be asked to consume two capsules (i.e. the daily dosage) of the allocated supplement. Two hours after consumption, additional measurements of FMD, blood pressure, vasomotion and certain biochemical parameters will be taken ( $T_A$ ).

In preparation for the follow-up assessments, participants will be asked to collect a 24-hour urine sample and 24-hour blood pressure will be measured. Bottles for urine collection and blood pressure monitors will be provided.

Following each intervention period, participants will undergo a washout period during which they will be asked to refrain from consuming high flavonoid-containing foods. During the whole study period, participants will be asked to keep a short diary of certain food records and illnesses. Although participants will be asked to refrain from consuming flavonoid-rich foods, if it so happens that a participant does consume a flavonoid-rich food, they will be asked to record this in the diary. In addition, they will also be asked to monitor and report symptoms of illnesses. As an extra measurement of compliance, participants will also be asked to report days in which they forget to consume the supplement. In order to aid compliance, two weeks' worth of capsules will be provided in a blister pack (Memory Pac, Unit Dose System).

#### *Intermediate Measurements:*

Every two weeks participants will be asked to visit the university in order to record their weight, take a blood sample and (if necessary) receive additional supplements for the following two weeks. These intermediate measurements will primarily be planned to keep participants actively involved in the study as well as to measure compliance and monitor health status (liver and renal function as well as whole blood cell count). Participants will be asked to bring all leftover supplements with them, thereby giving an indication of compliance. In addition, a blood sample will be taken and will be analysed to determine the level of plasma flavonoid metabolites.

*Part 2 (Cocoa Study):*

Four weeks after completion of the last intervention arm, participants will be asked to take part in Part 2 of the study. Part 2 will be optional and participation will not be obligatory for the participants. Those who opt to take part in Part 2 will be asked to return to the university on two different mornings – separated by two weeks. Measurements of vascular and endothelial function will be taken before and two hours after consumption of either a high or a low-flavanol cocoa beverage. These measurements will be used to compare the effects of pure epicatechin and epicatechin in cocoa on FMD and will also serve as positive control for FMD. Blood samples will also be taken for analysis of nitric oxide and plasma flavonoid concentrations .

### 6.3 Randomisation and Blinding

*Randomisation:*

Subjects will be sequentially randomly allocated to the various intervention arms based on their allocated treatment sequence (see table 5.1). Due to the fact that there are three intervention arms, six possible treatment sequences exist . Allocation to treatment sequence will be performed by an independent investigator employed at Wageningen University, who is not involved in the study. To maintain confidentiality, this investigator will be provided with an identification number for each participant and will not come into contact with the participants. At the start of each intervention period, another researcher will provide the participants with the materials needed for their allocated intervention. This researcher will not be involved in the collection of anthropometrical, physiological or biochemical data.

Table 5.1. Possible treatment sequences for the FLAVO-study.

| Treatment sequence |             |             |             |
|--------------------|-------------|-------------|-------------|
| 1                  | Placebo     | Epicatechin | Quercetin   |
| 2                  | Placebo     | Quercetin   | Epicatechin |
| 3                  | Epicatechin | Placebo     | Quercetin   |
| 4                  | Epicatechin | Quercetin   | Placebo     |
| 5                  | Quercetin   | Epicatechin | Placebo     |
| 6                  | Quercetin   | Placebo     | Epicatechin |

*Blinding:*

Researchers and medical staff will remain blinded towards the intervention. The company providing the capsules for the intervention (Het Gelre Apotheek, Apeldoorn) will be asked to deliver the capsules with a specific code for each treatment. The company will be asked to keep a record of the coding and will provide this code upon completion of the study. In case of serious adverse events, a subject's GP may request unblinding of the treatment.

Upon completion of the study, subjects will be asked to report the sequence of intervention groups they thought they had been allocated to. In addition, all subjects will be informed of the correct sequence of interventions they were allocated to – this will be conducted by the same researcher who provided the subjects with their materials during the intervention.

## 6.4 Study Parameter Methodology

### 6.4.1 *Physiological Measurements*

FMD and EID: To reduce variation, Flow-Mediated Dilation (FMD) and Endothelium-Independent Dilation (EID) measurements will always be conducted by the same researcher. FMD will be measured at time points T0, TA, T1, T2 and T3. EID will be measured at T0, TA and T3.

FMD will be measured as the percentage change in artery diameter in response to 5 minutes of venous occlusion. After baseline images have been obtained during a 3-minute rest period, a blood pressure cuff (placed distal to the antecubital fossa) will be inflated to 200mmHg for 5 minutes – thereby causing **arterial** occlusion. Brachial artery images will be recorded by means of ultra-sonography for 5 minutes after deflation.

EID will be measured as the percentage change in artery diameter in response to sublingual nitroglycerin administration (400µg). EID will be measured in order to distinguish between the endothelium-dependent and endothelium-independent effects of the intervention. Subjects will be warned of the side-effects of nitroglycerin administration prior to the start of the study. Side effects may include headaches and dizziness. Subjects will be advised to rest for 15 minutes after administration and to avoid intense exercise immediately after the measurement.

The percentage change in FMD/EID will be calculated as follows:

$$\% \text{ FMD/EID} = \frac{(\text{maximum diameter} - \text{baseline diameter})}{\text{baseline diameter}} \times 100$$

Blood Pressure: Systolic and diastolic blood pressure (SBP and DBP respectively) will be measured at the information session, screening session and at time points  $T_0$ ,  $T_A$  and  $T_1$  during the study.

For each measurement, four automatic blood pressure readings will be taken at 2-minute intervals (DINAMAP® PRO 100). The first reading will be discarded and an average of the final three will be calculated. Central blood pressure (CBP) will only be measured at time points  $T_0$  and  $T_1$  - using the SphygmoCor CPV System (AtCor Medical, Australia). Ambulatory 24-hour blood pressure (Spacelabs Healthcare) will be measured during the 24-hour period before the start and end of each intervention arm.

Pulse Wave Analysis (PWA): Pulse Wave Analyses will only be conducted at time points  $T_0$  and  $T_1$ . This means that a total of six Pulse Wave Analyses will be conducted per subject. For each analysis, three measurements will be taken and the average will be used to calculate the final values.

A variety of variables will be measured using the SphygmoCor CPV System (AtCor Medical, Australia). PWA allows a non-invasive assessment of the cardiovascular system by applanation of a tonometer on the radial pulse. From this measurement, CBP, augmentation index (AIx), subendocardial viability ratio (SEVR) and ejection duration will be automatically calculated.

Pulse Wave Velocity (PWV): Using the same apparatus (SphygmoCor CPV System), PWV will be measured at the same time points as PWA. The tonometer will sequentially be placed on the right carotid and femoral arteries for 15 seconds at a time – from which the PWV will be calculated. For each artery, three measurements will be taken. The average of the three measurements will be used for the final PWV calculation. Measurements will be taken in a temperature-controlled room following at least 10 minutes of rest. The distance between carotid and femoral artery will be measured using an infantometer.

Microvascular Vasomotion: Vasomotion will be conducted at time points  $T_0$ ,  $T_A$ ,  $T_1$ ,  $T_2$  and  $T_3$ . Microvascular vasomotion provides an assessment of blood perfusion as a result of rhythmic oscillations in vascular tone in small vessels of the circulatory system (capillaries, arterioles and venules) and will be measured using a Periflux 5001 Laser Doppler System (Perimed AB, Sweden). In brief, a laser Doppler probe is attached to the back of the non-dominant hand which releases a beam of laser light. Moving particles, such as blood cells, alter the wavelength of the returning signal allowing for the calculation of the number and velocity of circulating blood cells.

### 6.4.2 *Anthropometrical Measurements*

**Body Weight:** Subjects will be weighed using a digital balance scale, accurate to 0.1kg. All participants will be asked to wear minimal clothing, remove shoes and empty their pockets for weighing. Subjects will be weighed at the screening and at time points T0, TA, T1/2, T1 and T2 during the study.

**Height:** Height will be measured during the screening session using a configured wall-mounted stadiometer accurate to 0.5cm. All participants will be measured during the screening; wearing no shoes, with their back against the wall and with their head in the Frankfurt plane.

### 6.4.3 *Biochemical Measurements*

Fasting blood samples will be collected at all time points. This means that a total of 14 samples will be taken during the study. At time points T0 and T1, 50ml of blood will be collected. At time points TA, T1/2, T2 and T3, 20ml of blood will be collected.

All blood samples will be collected by trained lab technicians. Based on these blood samples, various plasma biomarkers will be analysed. All participants will be informed about the possible risk of bruising as a result of venepuncture.

**Markers of Endothelial and Vascular Function:** Endothelin-1 and ADMA will be analysed by Ultra-Performance Liquid Chromatography Tandem Mass Spectrometry (UPLC-MS/MS). Von Willebrand Factor (vWF) will be determined in citrated plasma by means of ELISA. All other biomarkers will be analysed by an electrochemiluminescence detection system using multiarray technology (Meso Scale Discovery). These analyses will be conducted at the central lab (i.e. Department of Internal Medicine, Maastricht University), with the exception of nitric oxide (NO) which will be measured at the RIKILT Institute of Food Safety. This will be done based on the estimation of NO formed by chemiluminescence after the release of nitric oxide from nitroso compounds and nitrosated and nitrosylated species

**Renal Function:** Glomerular Filtration Rate (GFR) will be estimated using the Modification of Diet in Renal Disease (MDRD) equation. This will be done based on values obtained for serum creatinine.

The MDRD equation is as follows:

$$\text{GFR (ml/min/1.73m}^2\text{)} = 186.3 \times (\text{Serum creatine in mg/dl})^{-1.154} \times \text{age}^{-0.203} \times 1.212 \text{ (if patient is black)} \times 0.742 \text{ (if female)}$$

Serum Lipoproteins, Glucose and Screening Samples: From the collected plasma samples, total cholesterol and high-density lipoprotein (HDL) as well as glucose will be measured at an external lab – the Stichting Huisartsen Lab Oost (SHO) in Velp, the Netherlands. Samples during screening will also be analysed at SHO for RBC, WBC, PLT, HB, HT (complete blood count), Hb A1C as well as ALAT, ASAT and  $\gamma$ -GT ( for liver function) and serum creatinine and ureum (for renal function).

Gene Expression: RNA will be isolated from peripheral blood mononuclear cells (PBMCs) to determine the level of gene expression of markers of inflammation and endothelial function.

Insulin Resistance and Sensitivity: Fasting plasma insulin and glucose levels will be used to estimate insulin resistance and sensitivity using the Homeostasis Model Assessment (HOMA-IR). Plasma insulin concentrations will be determined by radioimmunoassay at Wageningen University.

Plasma Flavonoids: Plasma flavonoid concentrations will be determined by means of HPLC-electrochemical detection at the RIKILT – Institute for Food Safety.

Measurement of Compliance: Due to the short half-life of flavonoids in blood, both urine and plasma concentrations of flavonoid metabolites will be measured to assess compliance. Plasma and 24-hour urine samples will be collected before the start of the study and on the last day of each intervention period. Both samples will be analysed by High-Pressure Liquid Chromatography. Additional plasma samples will be taken every two weeks as well as before, and 2 hours after, consumption of the final supplement on the last day of each intervention period.

**6.5 Withdrawal of individual subjects**

Subjects can leave the study at any time for any reason if they wish to do so without any consequences. The investigator can decide to withdraw a subject from the study for urgent medical reasons.

**6.6 Replacement of individual subjects after withdrawal**

If subjects withdraw prior to the start of the first intervention arm, they may be replaced if an appropriate replacement can be enrolled in time. Subjects who withdraw after the start of the first intervention period will not be replaced.

**6.7 Follow-up of subjects withdrawn from treatment**

Subjects who wish to withdraw from the study will be asked about their reason for withdrawal and whether they would still be willing to attend a follow-up assessment despite stopping the intervention. These subjects will also be asked if they would be willing to remain on the university's list of potential study participants for future studies.

**6.8 Premature termination of the study**

The standardized operating procedure of the Division of Human Nutrition concerning premature termination of the study will be used.

## 7. SAFETY REPORTING

### 7.1 Section 10 WMO event

In accordance to section 10, subsection 1, of the WMO, the investigator will inform the subjects and the reviewing accredited METC if anything occurs, on the basis of which it appears that the disadvantages of participation may be significantly greater than was foreseen in the research proposal. The study will be suspended pending further review by the accredited METC, except insofar as suspension would jeopardise the subjects' health. The investigator will take care that all subjects are kept informed.

### 7.2 Adverse and serious adverse events

Prior to the start of the study, all participants will be screened based on a number of health factors. As such, subjects with a blood pressure greater than 160mmHg will be excluded from the study. If participation in the study results in an increase in blood pressure above 160 mmHg then the study physician ([name]) will contact the participant's general practitioner (GP). If the GP deems it necessary to withdraw the participant from the study, then they will be free to do so. Alternatively, if the GP prescribes blood pressure-lowering medication, the participant will also be removed from the study.

If abnormalities are reported based on blood analyses during the screening or after completion of the study, then participants will be informed.

Adverse events are defined as any undesirable experience occurring to a subject during the study, whether or not considered related to [the investigational product / the experimental treatment]. All adverse events reported spontaneously by the subject or observed by the investigator or his staff will be recorded. These adverse events will then be reported to the study physician who will determine if they are a result of the intervention or if they could have detrimental effects to the results of the study.

A serious adverse event (SAE) is defined as any untoward medical occurrence or effect that at any dose:

- results in death;
- is life threatening (at the time of the event);
- requires hospitalisation or prolongation of existing inpatients' hospitalisation;
- results in persistent or significant disability or incapacity;
- is a congenital anomaly or birth defect;

- is a new event of the trial likely to affect the safety of the subjects, such as an unexpected outcome of an adverse reaction, lack of efficacy of an IMP used for the treatment of a life threatening disease, major safety finding from a newly completed animal study, etc.

All SAEs will be reported through the web portal *ToetsingOnline* to the accredited METC that approved the protocol, within 15 days after the sponsor has first knowledge of the serious adverse reactions.

SAEs that result in death or are life threatening should be reported expeditiously. The expedited reporting will occur not later than 7 days after the responsible investigator has first knowledge of the adverse reaction. This is for a preliminary report with another 8 days for completion of the report.

### **7.3 Follow-up of adverse events**

All adverse events will be followed until they have abated, or until a stable situation has been reached. Depending on the event, follow up may require additional tests or medical procedures as indicated, and/or referral to the general physician or a medical specialist.

## 8. STATISTICAL ANALYSIS

Statistical analyses will be conducted based on the intention-to-treat principle. An additional per-protocol analysis will be conducted, however, the intention-to-treat analysis will remain leading. Researchers involved in the statistical analysis will remain blinded to treatment allocation. For statistical significance, a two-tailed p-value of 0.05 will be set.

All data collected during the study will be quantitative. Continuous variables will be expressed as means  $\pm$  standard deviation while categorical variables will be expressed in frequencies. Data will be tested for normality by visual inspection of Q-Q plots and histograms.

Basic descriptive analyses (including age, gender, BMI and blood pressure) will be carried out based on subject characteristics obtained during the screening and baseline measurements.

A repeated measures analysis of variance (ANOVA) will be conducted to compare differences in intraindividual responses to the treatments. Changes from  $T_0$  to  $T_1$  will be used to determine the chronic effect of the intervention. Changes from  $T_1$  to  $T_A$  will be used to determine the acute effects of the intervention. Additional paired t-tests will be carried out to compare baseline values ( $T_0$ ) of outcome measures.

For data that are not normally distributed, a nonparametric Friedman's rank test will be conducted. All statistical analyses will be carried out using the SPSS 19.0 or SAS 9.2 software packages.

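### The repeated-measures ANOVA named for this three-period crossover has no period term, and the protocol does not say how subjects with a missing period enter the leading intention-to-treat analysis

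*Protocol*

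**What the plan says.** Protocol section 8 fixes the main method: "A repeated measures analysis of variance (ANOVA) will be conducted to compare differences in intraindividual responses to the treatments". The T0-to-T1 change carries the chronic effect and the T1-to-TA change the acute effect. The fallback is also fixed: "For data that are not normally distributed, a nonparametric Friedman's rank test will be conducted". No period or sequence term is mentioned.

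On the analysis set, the same section says "Statistical analyses will be conducted based on the intention-to-treat principle" and "An additional per-protocol analysis will be conducted, however, the intention-to-treat analysis will remain leading". It does not define the intention-to-treat set, nor say how a subject with one or two of the three periods is handled. On software it says only "All statistical analyses will be carried out using the SPSS 19.0 or SAS 9.2 software packages", without naming a procedure.

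The design around this analysis is as follows:
- Section 6.3 notes that "six possible treatment sequences exist", and Table 5.1 lists them.
- Section 4.4 allows for about 10% dropout.
- Section 6.6 states: "Subjects who withdraw after the start of the first intervention period will not be replaced".
- Section 6.7 asks those who withdraw whether they would still attend a follow-up assessment.

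**The concern.** Using all six orders of three treatments lets treatment be separated from period. The model as named compares treatments within subject and does not use that. If the change score differs by period for reasons other than treatment, the difference stays in the error term, the standard error is too large and power is lost.

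The protocol gives one concrete reason why the change might differ. Flavonoid restriction starts one week before the first baseline and then continues (sections 3 and 6.2). The first baseline follows 1 week of restriction, the second 1 + 4 + 4 = 9 weeks and the third 9 + 4 + 4 = 17 weeks. Any continuing effect of the diet would fall mainly in the period-1 change.

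The second issue is incomplete subjects. Dropout is expected and not replaced, so some subjects will have one or two periods. Classical repeated-measures ANOVA, with one row per subject, and the standard Friedman test both need all three. Run that way, an analysis labelled intention-to-treat would be a complete-case analysis. Under sections 4.3 and 7.2, a subject whose systolic pressure exceeds 160 mmHg leaves if the general practitioner deems it necessary or prescribes blood-pressure-lowering medication. For the blood pressure endpoints, loss could therefore depend on the response itself.

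**Working it through.** **Inputs.** From section 4.4: SD of the treatment response 2.7, chronic effect 1.3 FMD points, acute effect 1.5, power 0.80, dropout about 10%, 40 enrolled. From section 8: "For statistical significance, a two-tailed p-value of 0.05 will be set". From Table 5.1: the six sequences. Not in the protocol, so assumed: a linear step of d FMD points per period in the change score.

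**The plan's own figures.** n = 7.9 × (SD/D)².
- Chronic: 7.9 × (2.7/1.3)² = 34.1, so 35 (stated 35). With dropout, 35/0.9 = 38.9, so 39 (stated 40).
- Acute: 7.9 × (2.7/1.5)² = 25.6, so 26 (stated 25).

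These reproduce to within one subject. With 10% dropout, 40 × 0.9 = 36 subjects complete.

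**Variance added by drift.** The period of epicatechin minus the period of placebo, over sequences 1 to 6 of Table 5.1, is +1, +2, −1, −2, −1, +1. The mean is 0 and the mean square is 12/6 = 2. Quercetin minus placebo gives +2, +1, +1, −1, −2, −1, again with mean 0 and mean square 2. The apparent variance of a paired difference is therefore 2.7² + 2d² = 7.29 + 2d².

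**Power.** Paired t-test, 36 completers, D = 1.3, two-sided 0.05, noncentrality 1.3 × √36 / SD = 7.8/SD, 35 degrees of freedom:

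| d | Variance | Increase | SD | Power |
|---|---|---|---|---|
| 0 | 7.29 | 0% | 2.70 | 0.80 |
| 0.25 | 7.415 | 1.7% | 2.72 | 0.80 |
| 0.5 | 7.79 | 6.9% | 2.79 | 0.78 |
| 1.0 | 9.29 | 27% | 3.05 | 0.70 |
| 1.5 | 11.79 | 62% | 3.43 | 0.60 |

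A shift of 1.0 confined to period 1 gives gaps −1, −1, +1, +1, 0, 0 and mean square 4/6 = 0.67. Variance rises by 0.67/7.29 = 9%, and power is 0.77.

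**Bias from unequal sequences.** 40 is not a multiple of 6. With a 7,7,7,7,6,6 split, the gaps sum to at most 1 + 2 + 1 − 1 = 3, so the bias is at most 3d/40 = 0.075d.

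**Simulation.** 1,500 trials per setting, 40 subjects, six near-balanced sequences, 10% random dropout, fixed subject effects, true effect 1.3. Power at two-sided 0.05:

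| d | Complete cases, no period | Complete cases, period | All observed periods, period |
|---|---|---|---|
| 0 | 0.817 | 0.812 | 0.819 |
| 0.5 | 0.793 | 0.801 | 0.813 |
| 1.0 | 0.727 | 0.805 | 0.815 |

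The Monte Carlo error of each power is about √(0.8 × 0.2/1500) = 0.01.
- Without a period term the estimates averaged 1.29 to 1.31, so there was no visible bias.
- At d = 1.0 without the term, the model's standard error was 0.507 against an actual spread of 0.462. With no true effect, the test rejected in 3.4% of runs instead of 5%. The harm is an overstated error. The simulated 0.73 is somewhat above the analytic 0.70 because the gaps are fixed by design and not random noise.
- Using all observed periods instead of complete cases, both with a period term, moved the standard error from 0.449–0.450 to 0.444–0.446, about one point of power.

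**The case against.** The strongest reply has four parts.

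1. **A statistical analysis plan may settle this.** Model terms and missing-data rules are often left to such a plan, and none is shown. That limits the point but does not remove it, because section 8 commits to a particular model and fallback, and a better one is available at almost no cost.

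2. **Drift may be small.** Each period has its own baseline, so a shift in FMD level that is the same at T0 and T1 cancels; only drift in the change counts. The protocol also limits drift: one researcher does all FMD measurements (section 6.4.1), visits are at the same time of day (section 3), and diet advice is constant after run-in. A step of 1.0 per period is a 2-point drift across the trial, more than the 1.3-point effect sought. All this stands. At 0.5 or below the loss is two points of power or less.

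3. **Complete-case use is not stated.** A reader might infer that the protocol restricts the analysis to subjects with all three periods and so contradicts its own intention-to-treat rule. It does neither in words. That is how the named methods usually run, but the software allowed can fit incomplete data. The conflict is conditional.

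4. **The lost subjects are budgeted for.** This also stands: 36 completers give 80% power. Dropping incomplete subjects does not inflate the error variance, and a subject with one period adds almost nothing to a within-subject contrast.

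Two further readings should be resisted. Raised blood pressure alone does not remove a subject; it depends on the general practitioner's decision. And the relative efficiency of Friedman's test under normality, (3/π) × 3/4 = 0.72, does not describe the planned use, since the protocol reserves that test for non-normal data.

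**Conclusion.** The point holds in a limited form. The analysis named in section 8 makes no provision for period in a design that allows it. Its cost depends on a drift the protocol does not quantify: nothing if there is none, about two points of power at 0.5 FMD points per period, and about ten points by formula (nine in simulation) at 1.0. The consequence is lost power and intervals that are too wide. False positives do not increase, and bias is negligible while sequences are near balanced.

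The treatment of incomplete subjects is unspecified. If the methods are run in their usual form, the leading analysis becomes complete-case. That costs about one point of power when dropout is random, as the simulation assumed. The more serious risk, which the simulation does not measure, is bias if withdrawal relates to response, most plausibly for blood pressure.

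The power figures use two-sided 0.05 as in section 8. Section 4.4 cites 0.025; at two-sided 0.025 the values for d = 0, 0.5 and 1.0 are 0.71, 0.68 and 0.59, a similar pattern from a lower start.

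**What to change.** Replace the model in section 8 with a linear mixed model on each period's change (T0 to T1 for chronic, T1 to TA for acute), with fixed treatment and period and a subject effect. Include every observed period of all randomised subjects. Report the active-minus-placebo contrasts with confidence intervals. Say how subjects with missing periods enter the intention-to-treat set, including whether a follow-up assessment attended under section 6.7 supplies that period's outcome. Keep Friedman's test as a sensitivity analysis.

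The cost is a change of wording and two degrees of freedom for period. With no drift the term costs about one point of power at most (0.817 against 0.812 in simulation), and using all observed periods recovers about as much. Both named packages can fit the model. It protects against bias when withdrawal depends on outcomes already observed and modelled; it does not cure loss that depends on unobserved values.
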